### Outcomes

#### Primary Outcome

We aim to investigate the association between the volume of the left and right caudate nuclei and the size of the area of secondary hyperalgesia induced by brief thermal sensitization. The association will be expressed in adjusted and non-adjusted R^2^and prediction intervals for the area of secondary hyperalgesia, given fixed values of the caudate nucleus’ volume.

#### Secondary Outcomes

We aim to investigate the association between cortical and subcortical brain areas relevant for pain processing and the area of secondary hyperalgesia (primary somatosensory cortex, anterior- and mid-cingulate cortex, basal ganglia [putamen, accumbens nucleus, and globus pallidus], insula, and the cerebellum [12,42]). We will also use diffusion tensor imaging to investigate the association between the area of secondary hyperalgesia and white matter microstructure using tract based spatial statistics (TBSS) [43], and determine the connections between the pain-related areas, as specified previously using white-matter tractography.

#### Exploratory Outcomes

We will investigate the association between the volume of the left and right caudate nuclei and the following six parameters: (1) HPDT score, (2) p-TS max, (3) p-TS visual analog scale-area under the curve (VAS-AUC), and (4) the score of PCS-total, PCS-subscores, HADS-total, and HADS-subscores. When comparing healthy volunteers with a large (upper quartile) versus small (lower quartile) area of secondary hyperalgesia following BTS, we plan to investigate (5a) structural differences (volume) and the association with the size of the area of secondary hyperalgesia, (5b) differences in the association between area of secondary hyperalgesia and regions of interest extracted from TBSS, and (5c) differences in white matter microstructure in connections between pre specified pain related areas by white-matter tractography. In addition, we will examine (6) differences in resting state networks measured by rs-fMRI using independent component analysis (ICA; dual regression method).

### Hypothesis

The area of secondary hyperalgesia and the volume of the caudate nuclei are associated, with an inverse correlation (ie, a large area of secondary hyperalgesia is associated with a small volume of the caudate nuclei).

### Sample Size Estimation

Based on results from a previous study [11], sample size calculations are based on a Z-test of the Fisher transformed Pearson correlation. With a true correlation of r=-0.4 between the area of secondary hyperalgesia and the caudate nuclei, and a significance level of 2.5% to 5% according to the single step method (refer to *Statistical Significance*), a sample size of 52 is needed to obtain a power of 0.80 (β=0.20).

### Data Analysis Plan

#### T1-Weighted 3D Anatomical Images

Anatomical images will be pre-processed using the FreeSurfer imaging analysis suite version 5.3. FreeSurfer is a semi-automatic software package that performs volumetric segmentation of cortical and subcortical structures [44-46]. All volumes will be adjusted for total intracranial volume, and will result in volume estimates (mm^3^). This analysis is performed to avoid possible confounding results due to differential head-size between participants. The size of the area of secondary hyperalgesia will be blinded until completion of the T1-weighted 3D anatomical image analyses.

#### Diffusion Tensor Imaging

Diffusion-weighted images will be pre-processed using the Functional Magnetic Resonance Imaging Brain Software Library (FSL) software package version 5.0. This analysis includes corrections of potential head movement and inspection of image quality. The resulting data will then be processed via dtifit and tract-based spatial statistic. The re-aligned images will then be fed into bedpostx for local modelling of diffusion parameters. Using bedpostx in conjunction with TBSS allows for the modelling of crossing fibers. The re-aligned images will be fed into probtrackx2 for tractography between the anatomical areas mentioned above.

#### Resting-State Functional Magnetic Resonance Imaging

Rs-fMRI scans will be analyzed using FSL MELODIC. Pre-processing steps will include spatial smoothing, motion correction, high pass filtering, and brain extraction. In the pre-processing steps we will apply ICA using predefined (no less than 60) ICA’s without automatic dimension detection. Rs-fMRI scans will be co-registered initially to the individual T1-weighted 3D anatomical scans (after neutral flipping and brain extraction), and subsequently to the Montreal Neurological Institute (MNI)-152 brain atlas using non-linear registration. A full quality assurance will be performed consisting of inspection of head movement (<3 mm and <3 degrees), acceptable co-registration, and inspection of image quality.

Rs-fMRI data will be analysed using a model-free ICA and the dual regression method, as described by Abou-Elseoud et al [47], to determine differences in network connectivities with the whole brain. Standard, published brain networks in healthy participants will be used to identify the different networks using publicly available datasets from the Oxford FSL Group publication [48]. Once we have run an ICA analysis, the resulting components will be spatially cross-correlated with Oxford’s templates to identify those that better match the canonical networks described in the Oxford FSL Group publication [48].

Noise reduction will be performed manually. Randomized command with 10.000 random computations will be performed with a design matrix consisting of the unpaired t-tests (predefined high responders vs. low responders, and repeated with area of secondary hyperalgesia as co-variate). Results will be displayed upon the MNI-152 normal brain atlas after dimension change as *P*<0.05 after correction for multiple comparisons. Activated areas will be identified semi-automatically.

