#### Statistical Analysis of Secondary Outcome #2

The exact values of white matter structure expressed as the diffusion coefficient (Fractional Anisotropy value) of the relevant pain related areas will be extracted, and separate statistical analyses will be performed. To test the association between the white matter microstructure extracted following analysis using TBSS/DTI and the area of secondary hyperalgesia, individual measures computed from the TBSS and DTI will be investigated by linear regression.

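### The stated rs-fMRI group design carries no participant-level head-motion term, so a network difference between responder groups could be a residual-motion artefact if motion differs by phenotype

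*Protocol article*

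**What the plan says.** The protocol article's data analysis section on resting-state fMRI handles head motion in three places.

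- Pre-processing: "Pre-processing steps will include spatial smoothing, motion correction, high pass filtering, and brain extraction".
- Quality assurance: "inspection of head movement (<3 mm and <3 degrees), acceptable co-registration, and inspection of image quality".
- Denoising: "Noise reduction will be performed manually". Its criteria are not given.

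The group-level model is then spelled out. The permutation test "will be performed with a design matrix consisting of the unpaired t-tests", comparing high with low responders, and is then repeated with hyperalgesia area entered as covariate. The statistical section on exploratory associations 5 and 6 adds an unpaired t-test, or a Mann-Whitney test if the data are not normal, and false-discovery-rate control for rs-fMRI. Neither section names a motion term or a comparison of motion between responder groups.

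For DTI, pre-processing includes "corrections of potential head movement and inspection of image quality". The analysis of secondary outcome #2 says that "individual measures computed from the TBSS and DTI will be investigated by linear regression", without a list of covariates. Under the primary outcome, the article says that all structural MRI analyses are adjusted for age.

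**The concern.** Realignment puts the images of one participant into register. It does not undo every effect of movement on the signal. A limit of 3 mm and 3 degrees removes gross movers, but those who pass can still differ in average motion. What remains can shift connectivity estimates.

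The test compares the upper with the lower quartile of hyperalgesia area. If men in one quartile move more in the scanner, the contrast contains a motion component, and the design matrix as written cannot separate it from a network difference. False-discovery-rate control does not help here, because it limits chance findings and not a confounded contrast.

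At stake is the reading of exploratory outcome 6, which the article assigns to a second publication. The article accepts the same principle elsewhere: it adjusts volumes for intracranial volume to avoid confounding by head size, and it adjusts structural analyses for age.

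**Working it through.** **Plan's own figure.** The article gives no number for motion or for the power of the rs-fMRI test. Its only sample-size figure is 52, for the primary correlation of −0.4 with power 0.80. With n = ((z₁₋α/₂ + 0.842)/atanh 0.4)² + 3, a two-sided α of 0.05 gives 47 and 0.025 gives 56, so 52 falls inside the stated α range. It is used here only for the group size: 52/4 = 13 per quartile.

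**Inputs**
- 13 against 13 participants and an unpaired t-test with 24 df, from the article.
- Two-sided 5% for a single test, taken as a simplification.
- *Assumed*: d, the standardised difference in mean residual motion between the groups, and r, the within-group correlation of motion with the connectivity measure.

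**Formula.** With no true network difference, the spurious standardised difference is d × r. The non-centrality is (d × r)/√(2/13), with √(2/13) = 0.392. The error rate is the two-sided tail of a non-central t with 24 df beyond 2.064.

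| d | r | d × r | non-centrality | error rate |
|---|---|---|---|---|
| 0 | any | 0 | 0 | 5.0% |
| 0.3 | 0.3 | 0.09 | 0.23 | 5.6% |
| 0.5 | 0.5 | 0.25 | 0.64 | 9.4% |
| 0.8 | 0.5 | 0.40 | 1.02 | 16.5% |

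**Cross-check by simulation.** 20,000 null data sets of 52 participants were drawn, with the quartiles formed on area and motion correlated with both area and connectivity.

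| motion–area | motion–connectivity | t-test as written | with motion column |
|---|---|---|---|
| 0 | 0.2 to 0.5 | 4.9–5.0% | 4.9–5.1% |
| 0.2 | 0.2 | 5.7% | 5.0% |
| 0.3 | 0.3 | 8.7% | 4.9% |
| 0.3 | 0.5 | 15.4% | 5.1% |
| 0.4 | 0.5 | 23.7% | 4.8% |

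The two calculations agree in pattern. Inflation needs both links, is small when they are weak, and disappears when motion is correctly measured and adjusted for. The last row shows that stronger assumptions give larger figures, so the upper end reflects what is assumed and is not an estimate for this study.

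**Price of the column.** The residual df fall from 24 to 23, and the critical t rises from 2.064 to 2.069.

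**DTI, for scale only.** With n = 52, motion correlated 0.2 with both area and fractional anisotropy gives a spurious correlation of 0.04. On the Fisher scale this is 0.04 × √49 = 0.28, an error rate of 5.9%. Correlations of 0.3 with both give 0.09, then 0.63, and 9.7%.

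**The case against.** The strongest reply is that nothing in the article links motion to this phenotype. The participants are healthy; chronic pain and recent analgesic use are exclusions. No pain test takes place on the scan day, which falls 2 weeks to 2 months after pain testing. The article itself calls it uncertain whether the phenotype relates to pain sensitivity. The 50 minutes are the whole experimental day, not the resting-state run. This stands: the link is an assumption, and without it the error rate does not move.

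Second, the plan is not without motion control. A reader might infer that motion is ignored, or that a motion difference *would* be reported as a network effect with no step able to catch it. The text does not support that. Motion correction, quality assurance and manual noise reduction, in an analysis using at least 60 independent components, may remove much of the artefact. What remains is narrower: no stated step compares or adjusts for residual motion *between* groups.

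Third, the error rates are for one uncorrected test. The plan declares significance after correction for multiple comparisons, and the inflation under that procedure has not been calculated. This also stands.

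Fourth, a reader might extend the criticism to DTI and treat secondary outcome #2 as wrongly specified. The article states no full DTI model, and it states the age adjustment once without repeating it under each outcome. Silence in a condensed article does not show that motion is left out.

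The rs-fMRI design is different. There the article enumerates the contents of the design matrix and names the covariate used in the repeat, so the absence of motion is part of what is stated.

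**Conclusion.** The point holds for exploratory outcome 6, and only in conditional form: if residual motion differs between the responder quartiles, a network difference under the stated design could be a motion artefact. Across the directly calculated scenarios, the per-test error at nominal 5% runs from about 5.6% (d = 0.3, r = 0.3) to 16.5% (d = 0.8, r = 0.5), and it is unchanged if motion and phenotype are unrelated. All values of d and r are assumed, the tests are single and uncorrected, and the groups are 13 against 13.

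This is an inexpensive improvement to an exploratory analysis, not a defect in the study's main result. The primary caudate-volume analysis is unaffected, and no error is established in the DTI regressions.

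**What to change.** In the resting-state section of the data analysis plan:

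1. Add each participant's mean relative displacement, as estimated by the motion-correction step, as a mean-centred nuisance column in the dual-regression design matrix, both in the group comparison and in the repeat with area.
2. Report results with and without this column.
3. Report the motion summary by responder group.

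The cost is one column, about a sentence of text and one residual degree of freedom. If motion is itself part of the phenotype, the column may remove true signal; reporting both versions makes that visible. Fixing this before the areas are unblinded also avoids a later choice about whether to adjust.

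For secondary outcome #2, state whether the DTI models include a motion estimate. If they do not, a sensitivity analysis with that covariate is suggested.

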### Study Participants

Healthy male volunteers will be included in the study. The study participants will receive information regarding possible risks and side effects, and will be provided with written and oral information concerning the study. The participants will receive €67 (US $74) for their participation in the study. Inclusion and exclusion criteria are presented in Table 1.

**Table table1:** Inclusion, and exclusion criteria.

Inclusion criteria	Exclusion criteria
Age ≥18 years and ≤35 years	Study participants who cannot cooperate to the test
Male sex	Study participants with a substance abuse, assessed by the investigator
Study participants who have a weekly intake of >21 units of alcohol, or a have consumed >3 units of alcohol within 24 hours before experimental day Speak and understand the Danish language Signed informed consent Have participated and completed the study: “*To determine the degree of association between Heat Pain Detection Threshold and area of secondary hyperalgesia following Brief Thermal Sensitization in healthy male volunteers”* (Clinicaltrials.gov Identifier: NCT02527395)	Study participants who have consumed analgesics within 3 days before experimental day Study participants who have consumed antihistamines within 48 hours before experimental day Study participants who have consumed antidepressant medication within 30 days before the study Study participants who have consumed prescription medicine within 30 days before the study Study participants with neurological illnesses Study participants with chronic pain
	Study participants with psychiatric diagnoses
	Study participants with eczema, wounds, or sunburns on the sites of stimulation
	Study participants with a Body Mass Index of >30 kg/m^2^ or <18 kg/m^2^
	Study participants with contraindications to MRI^a^
	Study participants that decline information regarding potential pathological findings in relation to the MRI
	Study participants that have any kind of trauma resulting in pain and administration of analgesics in the period between experimental pain testing and MRI scan
	Study participants that experience a head trauma in the period between the experimental pain testing and the MRI scan
	

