### Statistical Analyses

#### Statistical Analysis of Primary Outcome

The estimates of the volumes, from the T1-weighted 3D anatomical scans of the caudate nuclei (mm^3^), will be exported to a spreadsheet for regression analysis to assess the association between volume of caudate nuclei and secondary hyperalgesia areas. The association of the volume of the left and right caudate nuclei and the area of secondary hyperalgesia will be investigated by linear regression of the estimated best linear unbiased predictors (EBLUPS) on the individual volumes of the left and right caudate nuclei. The ability of the volume of caudate nuclei to predict individual variation in the area of secondary hyperalgesia will be investigated by linear regression on the EBLUPS as a function of the individual volumes of the caudate nuclei.

Significance of the caudate nuclei as a predictor will be assessed by analysis of variance (ANOVA) methods and the predictive ability will be quantified by summary of prediction error, including 95% prediction interval for the prediction of the size of the area of secondary hyperalgesia. Relevant examples will be presented illustrating how accurately the volume of the caudate nuclei predicts the area of secondary hyperalgesia in the individual participants or vice versa. The association will be expressed in R^2^and prediction intervals for the area of secondary hyperalgesia given fixed values of the caudate nucleus’ volume. All analyses of structural MRI data (both in the primary, secondary, and exploratory outcomes) will be adjusted for age.

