#### Statistical Analysis of Exploratory Associations #5-6:

Quantile-quantile plots and Shapiro Wilk’s test will be applied in assessment of normal distribution. If data are not normally distributed, Mann-Whitney U-test will be applied. If data are normally distributed, unpaired t-tests will be applied to investigate structural differences in brain volume, differences in white matter, and differences in rs-fMRI between the groups. To investigate potential differences in rs-fMRI, correction for multiple comparisons will be conducted by the MRI software using False-Discovery-Rate. Values of secondary hyperalgesia areas will be entered into the FSL-software, and a t-test will be performed.

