## Discussion

We plan to investigate the association between experimental pain testing parameters and the volume, connectivity, and resting state activity of pain-relevant structures in the brain. We have designed this study to investigate basic pain physiology in healthy pain-free individuals, and we aim to investigate if any basic characteristics in the pain-free individual predict experimental pain responses. Current knowledge of basic pain physiology in humans is still sparse, and in order to compensate for the many factors that can affect pain responses, we have chosen to include a very homogenous population, consisting of healthy male volunteers between the ages of 18 and 35. The strict inclusion criteria diminish the influence of factors related to differences in the brain’s structure and function (eg, sex, age). Thus, this study aims to investigate aspects of basic pain physiology in healthy male individuals, and relevant caution should be taken when applying the results in a more heterogeneous population.

Our hypothesis, as well as our sample size estimation, are based upon previous results from Asghar et al [11]. Moreover, we wish to investigate if the volume of the caudate nuclei is associated with the size of the secondary hyperalgesia areas, indicating that this structure may be involved in the processes of central sensitization. Decreased volumes of the caudate nuclei have been demonstrated in a wide array of chronic pain patients, suggesting that these patients have a decreased ability to suppress and modulate pain stimuli [15,16,20-23,25]. With this study we plan to investigate if healthy participants with low volumes of caudate nuclei have a higher degree of central sensitization, and thus may be at a higher risk of developing chronic pain conditions.

The results of this study may also be informative for future studies and trials in the clinical setting, where pain remains a serious problem for postoperative patients. Knowledge of predictive factors and baseline pain dispositions in patients awaiting surgery may improve the design of trials on postoperative pain interventions, and improve our knowledge of the mechanisms responsible for the development of acute and chronic pain.

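### The resting-state group model (exploratory outcome 6) has no age term, although the plan adjusts structural MRI analyses for age in the same participants and names age as a factor in brain function

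*Protocol article*

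**What the plan says.** All references are to the protocol article.

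- **Resting-state group model.** The Data Analysis Plan (Resting-State Functional Magnetic Resonance Imaging) gives the contents of the matrix: "design matrix consisting of the unpaired t-tests (predefined high responders vs. low responders, and repeated with area of secondary hyperalgesia as co-variate". Area is the only covariate named.
- **Second description of the test.** Statistical Analysis of Exploratory Associations #5-6 adds: "Values of secondary hyperalgesia areas will be entered into the FSL-software, and a t-test will be performed". Age is not mentioned. The same section assigns an unpaired t-test, or a Mann-Whitney test if normality fails, to the volume, white matter and resting-state contrasts alike.
- **Scope of the age adjustment.** Statistical Analysis of Primary Outcome states: "All analyses of structural MRI data (both in the primary, secondary, and exploratory outcomes) will be adjusted for age". This covers every outcome level but only one type of data.
- **Reason for caring about age.** The Discussion states: "The strict inclusion criteria diminish the influence of factors related to differences in the brain’s structure and function (eg, sex, age". The corresponding entry criterion in Table 1 is "Age ≥18 years and ≤35 years", in men only.
- **The groups.** Exploratory Outcomes defines them as "large (upper quartile) versus small (lower quartile) area of secondary hyperalgesia following BTS". Outcome 6 is "differences in resting state networks measured by rs-fMRI using independent component analysis (ICA; dual regression method".

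**The concern.** The plan treats age as worth adjusting for when the measurement is a volume, but leaves it out when the measurement is network connectivity in the same men. It gives no reason for the difference, and its own Discussion links age to function as well as structure.

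The comparison is observational. Responder status is read off each participant's area of secondary hyperalgesia, so nothing in the design balances age between the upper and lower quartiles. Permutation testing and multiplicity correction address chance findings, not confounding. Area as a covariate does not help either, because area is the trait that defines the groups.

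At stake is the interpretation of outcome 6: a network difference that partly reflects age could be credited to the pain phenotype. Under Ethics, the article says that outcomes 5 and 6 will share a publication, so the two sets of contrasts will be read side by side.

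**Working it through.** **1. Is the omission in the text?**

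| Analysis | Model as described | Age |
|---|---|---|
| Caudate and other volumes (primary, secondary, exploratory 1-4) | Linear regression | Adjusted, by the general sentence on structural data |
| Quartile contrasts of volume (outcome 5a) | t-test or Mann-Whitney | Promised by the general sentence, but neither test can carry a covariate |
| Resting-state, group version | Unpaired high versus low | None |
| Resting-state, repeated version | Area as covariate | None |

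The article lists the contents of the matrix and separately fixes the scope of the age adjustment. Followed as written, the resting-state analysis omits age. The third column of the second row is a related gap: for the structural quartile contrasts, the promised adjustment has no model to sit in.

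**2. How large could the effect be?** The plan gives no figure on this point to reproduce, so what follows is an illustration.

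Inputs from the plan:
- N = 52 (Sample Size Estimation). The Fisher z formula, n = ((z_α + z_power)/atanh 0.4)² + 3 with two-sided α and power 0.80, gives 47 at α = 0.05, 56 at 0.025 and 52 at 0.035. The planned 52 therefore reproduces within the stated range of α.
- Upper versus lower quartile: 52/4 = 13 per group, if all 52 are analysed and the predefined responders are these quartiles.

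Assumptions, not in the documents: normal variables, no true group effect, one uncorrected two-sided 5% test, and correlations r₁ (age with area) and r₂ (age with connectivity).

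Formulas:
- Mean gap in area between the outer quartiles = 2·φ(0.6745)/0.25 = 2 × 0.3178/0.25 = 2.54 SD.
- Age gap = 2.54·r₁. Bias in the connectivity contrast = 2.54·r₁·r₂.
- Standard error with 13 per group = √(2/13) = 0.392 SD.
- Type I error from the noncentral t with 26 − 2 = 24 df and noncentrality bias/0.392.

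Worked case, r₁ = r₂ = 0.3: age gap 2.54 × 0.3 = 0.76 SD; bias 0.76 × 0.3 = 0.23 SD; noncentrality 0.23/0.392 ≈ 0.58; type I error 0.087.

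| r₁ / r₂ | Age gap (SD) | Bias (SD) | Type I error, no age term |
|---|---|---|---|
| either zero | – | 0 | 0.050 |
| 0.1 / 0.1 | 0.25 | 0.03 | 0.050 |
| 0.2 / 0.2 | 0.51 | 0.10 | 0.057 |
| 0.3 / 0.3 | 0.76 | 0.23 | 0.087 |
| 0.4 / 0.4 | 1.02 | 0.41 | 0.169 |

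**3. Does an age term remove it?** A simulation of the same setting (6,000 runs per case) gave, without and then with age in the model: 0.057 and 0.051 at 0.2/0.2; 0.091 and 0.053 at 0.3/0.3; 0.167 and 0.045 at 0.4/0.4. With r₁ = 0 the rate was about 0.05 either way.

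**The case against.** The strongest reply is that the design already deals with age by restriction: men of 18 to 35 only, which is what the Discussion sentence is about. That sentence is not an admission that age is uncontrolled, and restriction does narrow the scope for confounding. But it does not settle the matter, because the plan still adjusts structural data for age in this same restricted sample.

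The second reply is that the harm rests on assumption. This stands. No correlation of age with area or connectivity is given; at 0.1 and 0.1 there is practically no inflation; and the figure of 0.17 needs both correlations to be 0.4, the size that the plan assumes for its primary effect.

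The third is that nuisance columns are detail that an article may leave to a fuller plan. That carries less weight here, since the article states what the matrix contains.

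A reader might also infer more than the documents support:
- *That outcome 6 has a false-positive rate of 6% to 17%.* The figures are for one uncorrected t-test. The plan specifies 10,000 permutations with multiplicity correction.
- *That chance imbalance is itself a harm.* With 13 per group and no age-area relation, an age gap above 0.5 SD arises in about 20% of studies (2 × (1 − Φ(0.5/0.392)) = 0.20). That is already part of the test's sampling error, and the long-run rate stays at 5%.
- *That structural and functional results could not be compared.* The plan sets out no formal comparison between them, and the structural quartile contrasts are themselves described by tests without an age term. Different adjustment makes the results harder to read together, no more.
- *That the diffusion analyses are unadjusted too.* White matter microstructure can reasonably be read as structural MRI data, so no error is shown there.

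**Conclusion.** The point holds as an inconsistency in an exploratory analysis. Both versions of the resting-state model omit age, the general age adjustment does not reach them, and the plan's own reasoning gives no ground for treating function differently from structure. Part of a network difference could reflect age, but only if age is related to both area and connectivity. The documents do not show that it is, so the size of any bias is unknown. The illustrative range of 0.05 to 0.17 rests on assumed correlations of 0.1 to 0.4 and 13 per group. The primary and secondary conclusions are not affected. This is a minor improvement, worth making because it is nearly free.

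**What to change.** 1. In the resting-state section of the Data Analysis Plan, add mean-centred age as a nuisance column to both versions of the randomise design matrix (the group contrast and the repeat with area).
2. In Statistical Analysis of Exploratory Associations #5-6, replace the plain unpaired t-test or Mann-Whitney test for the group contrasts of outcomes 5 and 6 with a linear model containing group and age, with permutation-based inference if the data are not normal. The age adjustment already promised for structural data can then actually be carried out.

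If the sponsor prefers to leave age out of the resting-state model, the plan should say why it is adjusted for in structural but not functional data.

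Cost: one residual degree of freedom in the group contrast (26 − 2 = 24 becomes 26 − 3 = 23 with 13 per group) and a few changed words. No new data are needed, since age is an eligibility criterion and already enters the structural models.

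### The rs-fMRI repeat, read literally, adjusts groups that appear to be defined by hyperalgesia area for area itself, and neither the tested contrast nor the sample is stated

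*Protocol article*

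**What the plan says.** Three places in the protocol article bear on this.

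- **Data Analysis Plan, Resting-State Functional Magnetic Resonance Imaging.** The permutation design matrix holds unpaired t-tests: "predefined high responders vs. low responders, and repeated with area of secondary hyperalgesia as co-variate". No cut-off for high and low responders is given here.
- **Exploratory Outcomes.** For outcomes 5a to 5c the comparison is between "healthy volunteers with a large (upper quartile) versus small (lower quartile) area of secondary hyperalgesia following BTS". Outcome 6, resting-state networks by ICA and dual regression, follows in a separate sentence that does not repeat the group definition.
- **Statistical Analysis of Exploratory Associations #5-6.** Outcomes 5 and 6 are handled together. Where normality is accepted, the plan is that "unpaired t-tests will be applied to investigate structural differences in brain volume, differences in white matter, and differences in rs-fMRI between the groups". The section closes with "Values of secondary hyperalgesia areas will be entered into the FSL-software, and a t-test will be performed".

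Taken together, the quartile groups most plausibly carry over to rs-fMRI.

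**The concern.** High and low responders differ in area because area defines them. Adding area to a two-group model asks whether the groups differ by more than their difference in area predicts. That is a test of departure from a straight line, whereas outcome 6 asks whether resting-state connectivity differs with hyperalgesia phenotype. An empty map from the repeat could be taken as no difference after adjustment, when the model could not have shown a linear association.

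The article assigns outcomes 5 and 6 to a second publication of their own, so this analysis would carry a good part of that paper.

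**Working it through.** **Inputs**
- N = 52 (Sample Size Estimation).
- Effect size: "With a true correlation of r=-0.4 between the area of secondary hyperalgesia and the caudate nuclei". This is the caudate-volume assumption. The article gives no rs-fMRI effect size, so its use here is borrowed.
- Groups: upper and lower quartile of area (Exploratory Outcomes), assumed to be taken within the 52. Then 52/4 = 13 per group, 26 in the contrast and 26 outside it.
- Test level: two-sided 5%, one test, no voxelwise correction (assumption).

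**1. The article's own figure.** n = ((z for alpha + z for power)/atanh(0.4))² + 3, with atanh(0.4) = 0.4236.
- Alpha 0.05: ((1.960 + 0.842)/0.4236)² + 3 = 46.7, so 47.
- Alpha 0.025: ((2.241 + 0.842)/0.4236)² + 3 = 56.0, so 56.
- n = 52 corresponds to alpha of about 0.034, inside the stated range of 2.5% to 5%.

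The stated 52 therefore reproduces. No sample size or power is stated for the rs-fMRI test.

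**2. The adjusted group term.** Suppose connectivity = a + b × area + error. In a model with group and area together, the slope b absorbs the whole association and the true group coefficient is 0, whatever the value of b. The test then rejects at its alpha level.

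**3. Collinearity, normally distributed area.**
- Mean of the upper quartile: 1.271 SD. Variance within a quartile group: 0.242.
- R² of area on group = 1.271²/(1.271² + 0.242) = 0.870, so r = 0.93.
- Variance inflation = 1/(1 − 0.870) = 7.7. In simulated samples of 13 versus 13 the mean was 8.7.

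**4. Simulated power.** N = 52, r = -0.4, 8,000 replicates per scenario. The skewed case is lognormal, exp(0.6Z), standardised.

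| Test | Normal area | Skewed area |
|---|---|---|
| Regression on area, all 52 | 84% | 81% |
| Regression on area, outer quartiles only, no group term | 80% | 76% |
| Quartile t-test, 13 versus 13, unadjusted | 74% | 61% |
| Area slope with group term kept, 13 versus 13 | 17% | 31% |
| Group term adjusted for area, 13 versus 13 | 5% | 5% |

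With normal area, the mean group difference falls from -1.00 SD unadjusted to -0.03 SD adjusted. At r = -0.6 the adjusted group term still rejects only 5% of the time. A separate run put the all-participant regression at 85%. The Fisher formula agrees: 0.4236 × √49 − 1.960 = 1.005, which is 84%.

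**The case against.** The strongest reply is that the wording need not mean a group term adjusted for area. In an FSL design matrix a covariate can itself be the tested regressor, and the #5-6 section speaks of entering area values and running a t-test without limiting this to the quartile groups. If the repeat is a regression on area in all participants, it is sound and leaves no one out. This stands as a possible reading, but the text does not settle it. What the Data Analysis Plan describes as repeated is the two-group t-test, and testing the area slope with both groups still in the matrix gives only about 17% power (31% if area is skewed). The reply works only if the group term is dropped, which is nowhere stated.

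Two stronger readings are tempting, and the document supports neither.

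- A reader might infer that the rs-fMRI analysis as a whole cannot detect the effect. Only the repeat is affected; the unadjusted t-test comes first and is untouched.
- A reader might infer that half the scanned participants are discarded. The quartile cut for rs-fMRI is carried over from neighbouring sections, and the article does not say whether quartiles are taken among scanned participants or in the parallel study. The primary and secondary analyses are regressions with no restriction to quartiles.

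It is also fair to say that an extreme-group contrast continues the design of the group's previous imaging study. For an exploratory outcome with no power target, choosing it is partly a matter of preference.

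**Conclusion.** The point holds for the repeat analysis of exploratory outcome 6. Read literally, and with quartile groups, its group term has power equal to alpha for any linear association. That result follows from the model and does not depend on r = -0.4. The area slope in the same matrix is a weak substitute.

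The loss from the unadjusted quartile contrast is moderate: about 10 points of power with normal areas (84% to 74%) and about 20 with the skewed areas simulated (81% to 61%). These percentages rest on the borrowed effect size, on quartiles formed within the 52, and on a single uncorrected test. They rank the options and do not estimate the power of the planned voxelwise inference.

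The contrast and the participants for the repeat are left open in wording that otherwise fixes the groups, the covariate and the number of permutations.

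**What to change.** Replace the repeat with a randomise model in which area is the continuous regressor of interest, in all participants with usable rs-fMRI, with age as a nuisance covariate and positive and negative contrasts on area. Do not adjust the area-defined group term for area. Keep the unadjusted high-versus-low t-test alongside, and state the cut-off and the reference sample that define its groups. If the full-sample regression was what was meant, say so in both the rs-fMRI data analysis section and the #5-6 statistical section.

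The cost is a different design matrix, with no new data. It also keeps area continuous, as the primary and secondary regressions do. The drawback is an assumed roughly linear relation, which the retained group contrast can help to check.
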